**Fig. 1 Fig1:**
[figure not shown]
Recruitment and study procedure *Note*. CAU=Care-As-Usual, MBI = Mindfulness-Based Intervention

### Sample size

#### Power calculation

Power analyses are based on the primary hypothesis that family MBI, relative to control, will lead to improvement in self-control (as measured by the BRIEF) at end of treatment. The BRIEF has shown modest to large effect sizes in MBI studies for clinical samples, including bipolar disorder [140][Cohen’s d effect sizes from 0.08–1.33 on self-report BRIEF] and adult ADHD [57][Cohen’s d effect size from 0.43 to 0.93 on self-report BRIEF]; [56][Cohen’s d effect size from 0.67 to 1.72 on self-report BRIEF]. Further, in previous work using the MYmind programme (unpublished data on a larger non-randomised waitlist-controlled pilot in youth with ADHD *N* = 195 families using parent-report BRIEF; see also [55][Cohen’s d effect size from 0.0 to 1.8 on parent-report BRIEF; 0.2 to 0.5 on teacher-rated BRIEF]), a moderate effect on the BRIEF was found. Therefore power calculations were based on a moderate effect size of 0.4. Power analyses were run using the software G*power 3.1 and based on the procedure by G. F. Borm, J. Fransen and W. A. Lemmens [141]. Using this method, the N per group is obtained from the N per group for t-test multiplied by the design factor (D). The design factor D = 1–r^2^, where r^2^ is the correlation between baseline and end of treatment on the BRIEF. We determined r using the data of a normative sample over a comparable time frame (six weeks): .86 [142]. As the period between baseline and end of treatment is slightly longer in this trial (around eleven weeks) the power analyses was conducted using a more conservative estimate of *r* = .76, hence D = 1–.76^2^ = .42.

Based on a power of 80%, a two-tailed test with α = .05 and an estimated effect size of 0.4, we need 100*.42 = 42 children in each group. Past studies conducted using the MYmind programme (see section *Intervention*) using non-randomised designs in youth with ADHD and ASD found attrition rates from 5 to 15%. Therefore, we will recruit a slightly larger sample (2xN = 50, total *N* = 100), allowing room for attrition of around 15%.

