MYmind consists of eight weekly 90-min group sessions for children (groups of approximately 5–8), and parallel group sessions for their parents of equal length and duration. The child and parent sessions take place in separate rooms, with the exception of sessions 1, 5 and 8, where part of the session is together in the same room. In the sessions (playful) mindfulness exercises are done and education is given around the following themes, one per session: 1) Beginners’ mind, 2) Home in our body, 3) The breath, 4) Distractors!, 5) Stress, 6) High way, walking way, 7) Acceptance & autonomy, and 8) The future. Both children and parents receive daily homework during the eight weeks of training (15 min for child and 30–45 min for parent, 6 days/week). Theory and exercises are described in a workbook that both children and parents receive together with audio-files to guide the mindfulness exercises. As children with ADHD may have motivational problems, a reward system is incorporated in the course for the children to enhance motivation to practice in the sessions and at home. The 8-week course is followed by eight weeks of home self-practice, and a single joint child-parent 90-min booster session. In the booster session, participants share experiences of the mindfulness practice in the last eight weeks where they did not have the support of the group training, rehearse certain practices in order to remind the families of the possible joys and benefits of mindfulness practice, and are encouraged to think about how to implement mindfulness in their lives and to renew their intentions. Participants who attend four or more sessions will be considered as ‘completers’.

The first trial on an MBI for children combined with Mindful Parenting was conducted by Bögels et al. (2008) [64], which resulted in the MYmind training. Since then, several non-randomised pilot studies have been conducted with the MYmind training in child and adolescent samples with ADHD [54, 55, 65–67] and with ASD [68, 69]. Findings are promising and show that the MYmind training is feasible and acceptable [70].

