### Statistical analyses

Data will be analysed and reported according to CONSORT guidelines. Baseline demographic and clinical characteristics of the family MBI- and CAU-groups will be compared to examine whether these have been distributed evenly across the two groups by the randomisation. The primary analyses will be aimed at comparing results on the outcome measures at end of treatment between the family MBI and CAU condition, controlling for baseline levels and possible other baseline differences between intervention and CAU groups. To test our primary hypothesis that assignment to family MBI (relative to CAU) will improve child self-control, we will use ANCOVA with group condition (family MBI versus CAU) as the primary independent variable, and child self-control (continuous BRIEF-P score) at end of treatment as the primary dependent variable and child self-control at baseline as covariate. Cohen’s d effect sizes will be calculated. Analyses will be conducted both according to intention-to-treat principle, and per-protocol on completers (family MBI condition: child and parent attended > = 4 family MBI sessions). Intention-to-treat analyses will be conducted using available case analysis (not considering individuals with missing data) as well as imputation, as described in [145]. In case both parents participate in the assessments, data of the parent with the most complete dataset will be used for the ANCOVA, and if both are complete, the sex of the parent (or age, for same-sex parents) will determine which dataset will be used so that the fathers:mothers ratio is most similar across both study arms.

Secondary analyses, aimed at examining the consolidation of treatment effects at follow-ups, will use multilevel modelling with time point as repeated measurement, following the approach described in [58]. Moreover, we will conduct a set of complementary analyses to derive prediction models for response to intervention from baseline characteristics, and explore interactions between child and parental outcomes.

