This protocol describes an adequately powered RCT studying family MBI as an innovative non-pharmacological approach in the treatment of youth with ADHD. Children with comorbidities (e.g. ASD, ODD, dyslexia) will be included which has the advantage of increasing the representativeness of the sample for the clinical ADHD population. Where previous studies were uncontrolled or waitlist controlled, the current trial allows comparison with a CAU control group. Actually received CAU prior to and during study participation will be registered in both the control and intervention condition. The intervention is a manualised family MBI (MYmind) for children and their parents given by well trained experienced mindfulness teachers who will be evaluated in terms of both their adherence to the protocol and competence. Another strength of the study is that assessments will be done with different informants allowing taking account of rater effects. Questionnaires will not only be rated by self and parents, but also by teachers who are not involved in the intervention. Next to subjective ecologically valid questionnaires, objective computerised tasks will be administered to explore effects on different aspects of self-control. Further, a broad range of outcomes (e.g. neuropsychological functions, clinical symptoms, positive health) will be assessed in both the child and the parent. This not only allows studying the effect of family MBI on child and parental outcomes but also how they relate to each other. This will increase our understanding of the influence of parental symptoms, functioning and well-being on the child and vice versa, and the possible role that MBI on a family level may play in targeting child and/or parental needs. In addition, follow-up assessments until six months after the end of treatment make it possible to investigate both the short- and long-term effectiveness of the intervention. In a similar trial of an MBI in adults with ADHD, significant effects on self-control assessed with the BRIEF were only found at follow-up [58], as it might take more time and practice before MBI results in improvement of real-life self-control skills. Effects of self-control are suggested to follow a continuum, therefore interventions that achieve even small improvements in self-control for individuals, could shift outcomes across the population as a whole in a positive direction to impact health, wealth and crime rates [1]. Finally, ADHD is one of several psychopathologies (e.g. ODD, CD, addictions, mood- and anxiety disorders) that involve self-control deficits. Hence, results of the proposed RCT are in a cross-disorder perspective informative for a broad clinical population.

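### Neither the sample size nor the primary ANCOVA allows for clustering by MYmind group, although the intervention arm is treated in groups of about 5–8 children

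*Protocol article*

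**What the plan says.** Protocol article, *Study design*: families are randomised individually, 1:1, to MYmind plus care-as-usual (CAU) or to CAU alone.

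*Family MBI (MYmind)*: the course consists of weekly "group sessions for children (groups of approximately 5–8), and parallel group sessions for their parents". The *CAU* section describes no such groups for the control arm.

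*Power calculation*: "Based on a power of 80%, a two-tailed test with α = .05" and a standardised effect ("Therefore power calculations were based on a moderate effect size of 0.4"), the section takes the t-test size and multiplies it by one factor: "Using this method, the N per group is obtained from the N per group for t-test multiplied by the design factor (D"). That factor is the baseline-correlation one, "hence D = 1–.76^2^ = .42", and the result is "we need 100*.42 = 42 children in each group". Fifty per arm are recruited to cover about 15% attrition.

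*Statistical analyses*: for the primary hypothesis, "we will use ANCOVA with group condition (family MBI versus CAU) as the primary independent variable", with end-of-treatment BRIEF-P as the dependent variable and baseline BRIEF-P as covariate. Other baseline differences may also be controlled. Multilevel modelling is named only for the follow-up analyses, and the level given there is time point.

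*Discussion*: "This protocol describes an adequately powered RCT".

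**The concern.** This is a partially nested design. In the MYmind arm the child shares a teacher, sessions and peers with the rest of the group, and the participating parent attends a parallel group. The primary outcome is rated by a parent, so both the treated child and the rater may carry a common group influence. CAU families carry none. If outcomes within a MYmind group are correlated, the ANCOVA standard error is too small and the information in 42 treated children is less than the formula assumes.

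Baseline adjustment does not protect against influences that arise during the course, and it enlarges their share of what remains. With r = .76, a group effect worth 2% of total BRIEF-P variance is .02/.4224 = 4.7% of residual variance, and 5% of total becomes 11.8%.

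Two things are at stake: a primary test that declares MYmind effective too readily, and a power claim that rests on an unstated assumption of no group effect. Because the article itself fixes the formula and the model, this is not a detail left to an unseen analysis plan.

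**Working it through.** **Inputs from the protocol.** d = 0.4, two-sided α = .05, power 80%, r = .76, 42 analysed and 50 recruited per arm, attrition 5–15% (*Power calculation*); group size m of about 5–8 (*Family MBI (MYmind)*). **Assumed:** baseline-adjusted ICC in the MYmind arm of 0 to .10, because none is given. An ICC of .05–.10 of residual variance corresponds to .05 × .4224 = 2.1% to .10 × .4224 = 4.2% of total variance.

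**1. The protocol's own figure.** The t-test size for d = 0.4 is 99.1 per group, rounded to 100. D = 1 − .76² = .4224, and 100 × .4224 = 42.2. Directly, 2 × .4224 × (1.960 + 0.842)² / 0.4² = 41.4, so 42. Recruitment is 42/.85 = 49.4, so 50. With independent children, SE = √(2 × .4224/42) = .1418, 0.4/.1418 = 2.820 and power = Φ(2.820 − 1.960) = 80.5% (79.6% by t-test). The arithmetic reproduces. Slack is minimal: 50 × .85 = 42.5 against 42.

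**2. Clustering in one arm.** With DE = 1 + (m − 1) × ICC,

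Var(difference) = D × (DE/42 + 1/42).

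The true variance is therefore (DE + 1)/2 times the assumed one, not DE times. The type I error of the planned test is 2[1 − Φ(1.96/√((DE + 1)/2))].

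- m = 5, ICC .05: DE = 1.20, SE = .1487, 0.4/SE = 2.689, power 76.7%. Type I error: 1.96/√1.10 = 1.869, so 6.2%.
- m = 8, ICC .10: DE = 1.70, SE = .1648, 0.4/SE = 2.427, power 68.0%. Type I error: 1.96/√1.35 = 1.687, so 9.2%.

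**3. Few groups.** With 42/m groups (about 5 to 8), Satterthwaite degrees of freedom run from about 22 (m = 5, ICC .05) to about 10 (m = 8, ICC .10).

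Results at 42 per arm, ranges over m = 5 to 8:

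| ICC (assumed) | Power of a valid test, normal approx. | Same, Satterthwaite df | Type I error of planned ANCOVA |
|---|---|---|---|
| 0 | 80.5% | 75.2–77.4% | 5.0% |
| .01 | 79.2–79.7% | 73.4–76.5% | 5.2–5.4% |
| .05 | 74.0–76.7% | 66.8–72.9% | 6.2–7.1% |
| .10 | 68.0–73.1% | 59.5–68.8% | 7.4–9.2% |

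The ICC 0 row shows that about 3–5 points of each Satterthwaite figure are a degrees-of-freedom penalty, not clustering. Simulating the planned ANCOVA (8,000 runs per setting) gave type I error of 5.9–6.9% at ICC .05 and 7.1–9.5% at ICC .10, in line with the formula.

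**4. Lower attrition.** Ranges over m = 5 to 8:

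| Analysed per arm | ICC | Normal approx. | Satterthwaite df |
|---|---|---|---|
| 47.5 (5% loss) | .05 | 79.0–81.6% | 73.1–78.5% |
| 50 (no loss) | .05 | 81.0–83.5% | 75.6–80.7% |
| 47.5 (5% loss) | .10 | 73.3–78.2% | 66.0–74.6% |
| 50 (no loss) | .10 | 75.4–80.2% | 68.6–76.9% |

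**5. Size for 80% power** (normal approximation, equal arms): 43 analysed per arm at ICC .01, 46–49 at .05, 50–56 at .10.

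**The case against.** A reader might infer that the trial is underpowered and its p-value wrong as a matter of fact. The documents do not support that. Both consequences need an ICC above zero, and no ICC is given. At zero nothing is lost, and at .01 the loss is about one point by normal approximation. This stands.

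It can also be said that the planned ANCOVA keeps roughly its stated rejection rate under clustering. It does: at 42 per arm and ICC .05–.10 it still rejects in about 77–79% of trials by approximation and 76–79% by simulation. For the test as written the fault is the type I error. The lower power figures belong to a test that respects the clustering. They are still the relevant ones, because a rejection rate obtained at 6–9% type I error is not power at 5%.

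The protocol has some margin. Attrition may be nearer 5%, the drop-out questionnaire collects BRIEF-P, imputation is planned, and r was lowered from .86 to .76 on purpose. At ICC .05 and low attrition, power is indeed close to 80% by normal approximation. None of this corrects the standard error.

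It is also tempting to say that baseline adjustment cannot help because groups form after baseline. The protocol does not say when groups are composed. Randomisation precedes baseline, and baseline falls in the two weeks before the course. Similarity due to composition (site, school stage) could be present at baseline and partly adjusted away. Only effects arising during the course escape adjustment.

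Finally, a group variance is hard to estimate here. With seven groups of six, the analysis-of-variance estimate is zero or negative in about 39% of trials at ICC .05 and 52% at .01. That stands as a cost of the remedy.

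**Conclusion.** The concern holds in conditional form. Group delivery in one arm, a sample-size formula with no clustering factor and a primary model with no group term are all fixed in the article. For any positive ICC the direction is certain: the planned test is anti-conservative and a valid test has less power than calculated.

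The size depends on the assumed ICC. At .05–.10 it is material, with type I error of about 6–9% and valid-test power of about 68–77% by normal approximation, or about 60–73% with small-sample degrees of freedom. At .01 it is small on the normal approximation. These figures assume 42 analysed per arm, groups of 5–8, equal total residual variance in both arms, and the protocol's own d and r. The claim of adequate power therefore holds only if group variance is close to nil or attrition is low, and the protocol states neither as a condition.

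**What to change.** Keep N = 100 and change the analysis and the stated power.

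- **Primary model.** Use a baseline-adjusted partially nested mixed model: a random intercept for MYmind group in the intervention arm only, with Satterthwaite or Kenward–Roger degrees of freedom. State in advance what is reported if the group variance is estimated at zero, for example whether group-based degrees of freedom are retained.
- **Parent outcomes.** Use the same structure, since parents are also treated in groups.
- **Sample-size section.** State the ICC assumption, give power as a range over ICC and over 0–15% attrition, and say which degrees of freedom the figures use.
- **Discussion.** Qualify the statement "This protocol describes an adequately powered RCT" accordingly.

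Recruitment and outcome assessments do not change; the model needs only each family's MYmind group. The costs are wider confidence intervals, a less favourable stated power (including the 3–5 points lost to degrees of freedom even if the ICC is zero), and an imprecise group-variance estimate from only about 5–10 groups.

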### Randomisation

Randomisation by means of minimisation [143] will be performed after completion of the informed consent forms. The treatment group that most strongly minimises the imbalance between the two conditions is chosen to allocate the patient. To balance possibly prognostic factors across treatment groups, the following procedure will be performed: first, a stratification for age group is performed (elementary school or secondary school). Then, block randomisation is performed (with varying predefined block sizes), combined with minimisation. The three minimisation factors are: 1) medication for ADHD at baseline (medication versus no medication); 2) gender (male versus female); and 3) age (younger (child: age 8–10 or adolescent: age 12–14) versus older (child: age 10–12 or adolescent: age 14–16)). Minimisation factors are of equal importance, and block randomisation always wins over minimisation. Concealment of allocation is guaranteed as the sequence behind the randomisation will be unknown by the executing researcher.

### Data collection, management analysis

As soon as the participant is enrolled, across all assessments he or she will only be identifiable via a unique pseudocode identifier to anonymise all data. A separate protected data-base will link the unique pseudocode to the participants’ names. Anonymous and non-anonymous (e.g. informed consent forms) data will be stored in separate password protected folders. Video-data of the sessions will be transported with an encrypted external hard disk and stored on a network attached storage only accessible for the appointed researchers. Questionnaire data will be collected and stored with the online electronic data capture software CASTOR EDC [144], which tracks and logs any manual changes made to raw data and is fully Good Clinical Practice (GCP) compliant. Quantitative data that is first collected on paper (e.g. IQ test, diagnostic interview) will be manually entered in CASTOR EDC and the entry will be double checked by another researcher. To prevent missing data, the force step completion function will be used so informants can only continue with the questionnaire when all items are completed. When questionnaires are not completed within the expected period, participants/school teachers will be sent online reminders. If no response follows they will be contacted per telephone to discuss the absence of response and to motivate them to complete the questionnaires, if necessary with concessions (e.g. fewer questionnaires). In case participation is discontinued, reasons will be noted and participants will be asked to complete a drop-out questionnaire with the main outcome measures (BRIEF-P, BRIEF-A, CPRS and parental ADHD self-report). Clinically informative results derived from child- and parent-rated questionnaire data will be reported by the researchers and sent to the involved participant after study participation ends.

### Statistical analyses

Data will be analysed and reported according to CONSORT guidelines. Baseline demographic and clinical characteristics of the family MBI- and CAU-groups will be compared to examine whether these have been distributed evenly across the two groups by the randomisation. The primary analyses will be aimed at comparing results on the outcome measures at end of treatment between the family MBI and CAU condition, controlling for baseline levels and possible other baseline differences between intervention and CAU groups. To test our primary hypothesis that assignment to family MBI (relative to CAU) will improve child self-control, we will use ANCOVA with group condition (family MBI versus CAU) as the primary independent variable, and child self-control (continuous BRIEF-P score) at end of treatment as the primary dependent variable and child self-control at baseline as covariate. Cohen’s d effect sizes will be calculated. Analyses will be conducted both according to intention-to-treat principle, and per-protocol on completers (family MBI condition: child and parent attended > = 4 family MBI sessions). Intention-to-treat analyses will be conducted using available case analysis (not considering individuals with missing data) as well as imputation, as described in [145]. In case both parents participate in the assessments, data of the parent with the most complete dataset will be used for the ANCOVA, and if both are complete, the sex of the parent (or age, for same-sex parents) will determine which dataset will be used so that the fathers:mothers ratio is most similar across both study arms.

Secondary analyses, aimed at examining the consolidation of treatment effects at follow-ups, will use multilevel modelling with time point as repeated measurement, following the approach described in [58]. Moreover, we will conduct a set of complementary analyses to derive prediction models for response to intervention from baseline characteristics, and explore interactions between child and parental outcomes.

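### The primary covariate rule depends on observed imbalance, does not match the ANCOVA stated next, and leaves out the factors used for allocation

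*Protocol article*

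**What the plan says.** Protocol article, Statistical analyses. Baseline characteristics of the arms "will be compared to examine whether these have been distributed evenly across the two groups by the randomisation". The primary analyses are then described as "controlling for baseline levels and possible other baseline differences between intervention and CAU groups". No list of variables, test or threshold is given for deciding what counts as a difference. The following sentence specifies the test of the primary hypothesis: an ANCOVA with group as the independent variable, BRIEF-P "at end of treatment as the primary dependent variable and child self-control at baseline as covariate". No other covariate is named there.

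Protocol article, Randomisation. Allocation is stratified by school level (elementary or secondary) and blocked, with minimisation inside the blocks. The purpose is given as "To balance possibly prognostic factors across treatment groups". "The three minimisation factors are: 1) medication for ADHD at baseline (medication versus no medication); 2) gender (male versus female); and 3) age" in a younger and an older category. None of these four factors appears in any analysis model in the article.

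Protocol article, Power calculation. The sample size rests on an ANCOVA adjusted for baseline BRIEF-P alone, with a planning correlation of 0.76.

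**The concern.** Two things look wrong.

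First, the two consecutive sentences on the primary analysis do not define the same model. One admits further covariates according to what the baseline comparison shows; the other has baseline BRIEF-P only. After sound randomisation, a baseline difference is chance, and its size says nothing about whether the variable predicts outcome. A model that follows the first sentence is unknown until the data are seen.

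Second, the variables the article itself regards as possibly prognostic are in neither version. Allocation is built to keep them balanced, so a rule that waits for imbalance would seldom bring them in. Balancing a prognostic factor reduces the true variability of the treatment estimate, but a model that omits the factor does not credit that reduction. Its standard error is then too large, and some available power is not used.

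**Working it through.** **The plan's own figure.** Inputs from the Power calculation section: effect size 0.4, two-sided alpha 0.05, power 80%, r = 0.76, attrition about 15%.

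- The two-sample t-test needs 99 per arm (normal approximation) or 100 (exact noncentral t).
- Design factor: 1 − 0.76² = 0.4224.
- 99 × 0.4224 = 41.8 and 100 × 0.4224 = 42.2. The article states 42.
- 42 / 0.85 = 49.4, rounded up to 50. The article states 50.

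The sample size reproduces and is not affected by this point.

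**What to expect for the standard error.** In outcome SD units with 42 per arm, the baseline-only ANCOVA has SE = √(2 × 0.4224 / 42) = 0.142. If the four allocation factors explain a share R² of the residual variance and are perfectly balanced, the true SE is 0.142 × √(1 − R²). The model SE is then too large by a factor 1/√(1 − R²): 1.026, 1.054 and 1.118 at R² = 0.05, 0.10 and 0.20.

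**Simulation with imperfect balance.** There were 84 evaluable children, two school strata and blocks that override minimisation, as the article states. Each setting had 6,000 runs under no effect and 2,000 at d = 0.4. Assumptions not in the article:

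- R² from 0 to 0.20, shared equally by the four factors
- block sizes 4 and 6
- 70% on medication, 30% in one gender group, and even splits for age category and school level
- ten other baseline variables that together explain 10% of the residual variance

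| R² | Baseline-only: model SE | Baseline-only: true SD of estimate | SE too large by | Type I error, baseline-only | Type I error, factors included | Power, baseline-only | Power, factors included |
|---|---|---|---|---|---|---|---|
| 0 | 0.142 | 0.143 | none | 5.1% | 4.9% | 78.3% | 78.2% |
| 0.05 | 0.142 | 0.139 | 2% | 4.5% | 4.8% | 79.0% | 80.2% |
| 0.10 | 0.142 | 0.135 | 5% | 3.8% | 4.8% | 80.8% | 83.7% |
| 0.20 | 0.142 | 0.129 | 11% | 2.9% | 5.0% | 81.5% | 87.0% |

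Monte Carlo standard errors are about √(0.05 × 0.95 / 6000) = 0.3 points for type I error and √(0.8 × 0.2 / 2000) = 0.9 points for power. The 78.3% at R² = 0 is therefore compatible with the exact value of 79.6% for 42 per arm.

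**Does the imbalance rule repair this?** The rule was simulated by adding any of the ten other baseline variables with p < 0.05 between arms. Type I error was 4.8%, 4.2%, 3.5% and 2.7% at R² = 0, 0.05, 0.10 and 0.20, so it does not.

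**How open is the model?** If the comparison were k independent tests at 0.05, the chance of selecting at least one covariate would be 1 − 0.95^k: 23% for k = 5, 40% for k = 10 and 64% for k = 20. The article states neither a test, a threshold nor a count, so these figures are illustrations only. Free choice between the baseline-only and the selected model raised null rejection at R² = 0 from 5.1% to 5.6%.

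**The case against.** The strongest reply is that the primary model is already fixed. The loose clause sits in a sentence about outcome measures in general. The sentence that tests the primary hypothesis names baseline BRIEF-P alone, and the sample size is built on that same model. This reading is tenable, so a reader who infers that the primary covariates will certainly be picked from the data goes beyond the text. What stands is that the clause is worded as applying to the primary analyses and does not agree with the sentence after it.

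A second reply is that a condensed article may leave stratification covariates to the analysis plan, and nothing in it excludes them. Silence alone would not be a fault. Here, however, the article states a covariate rule and a model, and a plan that followed either would omit the four factors.

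A third reply concerns size, and it stands. The effect exists only if the factors predict outcome beyond baseline BRIEF-P, and with a planning correlation of 0.76 the baseline score may already carry much of what they predict. At R² = 0.05 the departure from 5% is within simulation error.

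A reader might also infer that omitting the factors yields false positives or an underpowered trial. Neither follows: the error is on the conservative side, and power of the baseline-only model stays close to the planned 80%. Nor is the benefit of balanced allocation lost. The estimate itself is less variable, and only the reported standard error fails to show it.

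**Conclusion.** The point holds as a matter of specification with a modest cost in efficiency. The two sentences on the primary analysis must be reconciled, and the four allocation factors belong in the model.

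The size depends on R², which the article does not give. The baseline-only standard error is right at 0 and about 2%, 5% and 11% too large at 0.05, 0.10 and 0.20. The power forgone is about 3 points at 0.10 (83.7 − 80.8 = 2.9) and 5 to 6 at 0.20 (87.0 − 81.5 = 5.5). The block sizes and factor prevalences behind these figures are also assumptions. The chance that a covariate gets selected, such as 64% with 20 tests, should not be read as an error rate of the trial. It assumes a procedure the article does not state, and the measured effect of choosing between models was about half a point.

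**What to change.** Prespecify one primary ANCOVA: end-of-treatment BRIEF-P on arm, baseline BRIEF-P, school level, ADHD medication at baseline, gender, and age in the younger/older category used for minimisation. Naming the form of age matters, since leaving it open would bring back an analyst's choice.

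Delete the clause on other baseline differences from the primary analysis, or keep such a model only as a labelled sensitivity analysis. Report the baseline tables descriptively, without using them to trigger covariates.

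The cost is wording. All four factors are collected for allocation, and the sample size does not change. With 84 analysed, residual degrees of freedom go from 84 − 3 = 81 to 84 − 7 = 77. If the factors turn out to predict nothing, the simulated power is essentially unchanged (78.2% against 78.3%).
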